## **2.6 Blinding**

The study will include a random assignment for volunteers into three groups. The volunteers will be blinded, not aware of which electrical stimulation mode will be used. The examiner will know about the study because it requires practice and knowledge with an electrical stimulator. The statistician will also be blinded to intervention allocation. The data will be coded in an unrecognizable manner, with no information indicating which group a single participant will be assigned to.

## **2.7 Sample size calculation**

The sample size will be based on a pilot study considering quadriceps torque as a primary outcome. The required sample size was calculated by assuming 80% power with a significance level of 0.05. To detect the minimum mean difference of 1.5 points and a standard deviation of 2.5 and considering a 10% dropout is the most suitable. [25]

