### **Primary outcome measure**

Considering the potential advantages of NMES for enhancing muscle performance and the dearth of research in this area, the main objective of this study will be directed to evaluate the impact of various Russian current expert modes on the maximum electrically induced torque of the quadriceps femoris, and to compare the electrically elicited knee extensor torque at the maximal stimulation tolerance level using 3 different RC experts' modes (off mode, on mode and on2 mode).

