positioned just above the ankle malleoli, while the lateral epicondyle of the knee will be in line with the axis of rotation of the lever arm. The participant's peak knee extension torque will be determined using an MVIC performed at 90° of knee flexion against the isokinetic dynamometer's resistance arm. After being correctly seated in the Biodex device, and prior to the application of stimulation, participants will be asked to perform a minimum of three maximum voluntary isometric contractions (MVIC). The participant is required to hold each contraction for around five seconds and rest for 120 seconds (about two minutes) in between each contraction. The highest peak torque generated during the three maximum-effort trials will be called KEMVIT, where the maximum volitional peak knee extensor muscle torque (Newton meters) will be recorded using a Biodex as a baseline measurement. For instance, if there is an increase in the maximum torque by more than 5% on the third attempt, the participants will be asked to continue the contraction efforts until the increase in maximum peak torque decreases to less than 5%. The peak torque produced during the testing will be used to normalize the RC-elicited knee extensor torque to produce a percent of KEMVIT (%KEMVIT), a verbal encouragement will be given to the participants by the examiner to promote maximal effort during all contractions.

In the same position used to determine the maximum torque, RC stimulation will be administered. Two channels will be used for delivering the electrical stimulus: On the anterior thigh, four circular cutaneous electrodes with a 7.6-cm diameter will be placed. The anode will be positioned distally over the vastus medialis, with the cathode being positioned proximally over the rectus femoris. Prior to beginning testing, participants will be instructed to relax during the electrical stimulation application so that all knee extensor torque production comes directly from the electrical stimulation rather than the quadriceps muscle voluntary contraction. Participants will be monitored and instructed to self-report pain on an 11-point (0–10) numeric pain-rating scale after each

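### The 80% power claim rests on a difference and SD with no stated torque scale, and 66 participants do not give 80% power for that 0.6 SD difference in any case

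*Protocol*

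**What the plan says.** Section 2.7 opens with "The sample size will be based on a pilot study considering quadriceps torque as a primary outcome". It then assumes 80% power and a significance level of 0.05, with the inputs "To detect the minimum mean difference of 1.5 points and a standard deviation of 2.5", and a 10% dropout allowance. It gives no unit for the SD, no pilot figures and no resulting sample size. The total of 66 in three groups appears only in the Methods part of the abstract.

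The primary outcome paragraph in section 2.4 concerns "the maximum electrically induced torque of the quadriceps femoris", compared across the three modes, and names no scale.

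Section 2.9 mentions two scales:
- For the voluntary contraction: "maximum volitional peak knee extensor muscle torque (Newton meters) will be recorded using a Biodex as a baseline measurement". This is KEMVIT.
- For the elicited torque, that voluntary peak is used to "normalize the RC-elicited knee extensor torque to produce a percent of KEMVIT (%KEMVIT").

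No sentence says which scale carries the primary comparison.

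**The concern.** Power depends on the target difference divided by the SD, both on the scale that is analysed. Here the outcome is named in one section without a scale, a scale for elicited torque appears in another, and the power inputs are in a unit that is tied to neither. A reader cannot tell whether 1.5 is a worthwhile difference in torque, or whether 2.5 is a plausible SD for it. The primary scale is also left open.

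The ratio of the two inputs needs no unit, so one part of the claim can be tested as it stands: whether 66 participants give 80% power at that ratio. If they do not, naming the unit alone would leave the power statement wrong. A null comparison between modes would then be read as stronger evidence than it is.

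**Working it through.** **Inputs from the protocol.** Difference 1.5, SD 2.5, power 80%, alpha 0.05 and dropout 10% (section 2.7); 66 participants in three groups (abstract, Methods).

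**Assumptions.** 1:1:1 allocation, two-sided alpha, and a t-test between two modes without multiplicity correction. The protocol states none of these.

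**Step 1: the unit-free ratio.** d = 1.5/2.5 = 0.6. This holds for any unit, provided both figures share it.

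**Step 2: can 66 be reproduced from the stated inputs?** With the normal formula for two means:

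n per arm = 2 × ((1.960 + 0.842)/0.6)² = 2 × 21.80 = 43.6, so 44.

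With 10% dropout, 44/0.9 = 48.9, so 49 per arm and 3 × 49 = 147 in total. The exact t-test needs 45 completers per arm (power 80.4%; 44 give 79.5%).

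Other routes to a total:

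| Calculation | Per arm | Total | Total with 10% dropout |
|---|---|---|---|
| Two means, two-sided | 44 | 132 | 147 |
| Two means, one-sided | 35 | 105 | 117 |
| Two means, alpha 0.05/3 | 59 | 177 | 198 |
| ANOVA, means 0, 0.75, 1.5 | 55 | 165 | 186 |
| ANOVA, means 0, 0, 1.5 | 42 | 126 | 141 |
| ANOVA, means 0, 1.5, 3 | 15 | 45 | 51 |
| One-sample or paired, ((1.960 + 0.842)/0.6)² | 22 | 66 | 75 |

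Only the last row gives 66. It does so without the stated dropout allowance, and it is the formula for a change within one group, not a comparison between modes. That this is where 66 came from is a guess.

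**Step 3: power at 0.6 SD with 66 participants.** Per arm 66/3 = 22; after 10% dropout 22 × 0.9 = 19.8. Completers are the right count, since section 2.8 says that the data of those who withdraw are destroyed. Noncentrality = d × √(n/2):

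| n per arm | Noncentrality | df | Critical t | Power |
|---|---|---|---|---|
| 22 | 0.6 × √11 = 1.99 | 42 | 2.018 | 49% |
| 19.8 | 0.6 × √9.9 = 1.89 | 37.6 | 2.025 | 45% |

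**Step 4: what 66 participants can detect.** Solving the same t-test for 80% power at 19.8 per arm gives d = 0.914. As a check, the normal approximation gives 2.802 × √(2/19.8) = 0.89. So the detectable difference is about 0.91 SD. If 2.5 is the right SD, that is 0.914 × 2.5 = 2.3 of the protocol's points, against the stated 1.5.

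**The case against.** **Points may be a torque unit.** Elicited torque is expressed as a percent of KEMVIT, and a difference between two percentages is naturally given in percentage points. Newton meters are attached to the voluntary baseline torque, which serves to normalise. So the likeliest reading may be 1.5 percentage points of KEMVIT with an SD of 2.5. This stands as a possibility: it would be wrong to say that points cannot describe torque here. But the protocol does not say it, and the power shortfall is the same on that reading.

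**A reader might infer that the inputs were borrowed from the pain scale,** because participants are "instructed to self-report pain on an 11-point" scale and 1.5 and 2.5 would fit a 0 to 10 rating. The documents do not support this. Section 2.7 names quadriceps torque, and only a shared word links the two. Nor can power for torque be worked out from some other SD: the protocol gives none, and assumed values would measure the assumption rather than the plan.

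**The unit does not change the arithmetic.** True, since the sample size depends only on the ratio. The unit decides whether that ratio means anything for the primary outcome; the shortfall is a separate step and holds for any unit.

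**A different analysis could do better.** If 2.5 is an unadjusted SD and the analysis adjusts for a baseline correlated 0.75 with the outcome, 44 × (1 − 0.75²) = 19.25, so 20 completers per arm, which 66 participants nearly supply. If 1.5 is the gap between neighbouring modes and the outer two differ by 3, the overall ANOVA has about 92% power with 20 per arm. Section 2.7 mentions neither a baseline correlation nor such a pattern of means, and under the second reading a pairwise difference of 1.5 still has about 45% power.

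**Conclusion.** The point holds in two parts. First, the 80% power claim is not tied to a defined primary endpoint, because the protocol gives no scale for the outcome in section 2.4 and no torque unit for the inputs in section 2.7. This is an unspecified unit, not proof that the figures belong to another outcome. Second, the claim fails on its own ratio: at 0.6 SD, 66 participants give about 45% power with the stated dropout and about 49% without, and 80% power is reached only at about 0.91 SD.

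The second part rests on equal allocation, two-sided alpha 0.05 and an unadjusted pairwise t-test. A correction for three comparisons would lower the power further (about 31% at 19.8 per arm by the normal approximation); a strong baseline adjustment would raise it. No corrected sample size for torque can be computed until the scale and its SD are stated.

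**What to change.** 1. In section 2.4, name one scale for the primary outcome, for example elicited torque as a percent of the participant's baseline KEMVIT.
2. In section 2.7, give the difference and the SD on that scale, with their source. If the pilot study supplies them, show the figures; the present text does not show that pilot data are in hand. If points does mean percentage points of KEMVIT, say so.
3. In section 2.7, replace the 80% power claim with what 66 participants deliver: about 0.91 SD between two modes at 80% power, or about 45% power at 0.6 SD. State the allocation ratio, sidedness and comparison assumed. If a baseline-adjusted analysis is intended, state the correlation relied on and recompute.

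The cost is a few sentences and one recalculation. With the total kept at 66, no extra participants are needed. The downside is that the stated power or detectable difference becomes less favourable. Keeping 80% power at 0.6 SD without adjustment would instead take about 147 participants.

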## **Methods**

This is a single-blinded, block-randomization controlled trial in a prospectively controlled laboratory. Sixty-six healthy university students will be recruited from the University of Sharjah, United Arab Emirates (UAE). The volunteers will be divided into three systemically randomized experimental groups. Each group will be admitted to a program of training utilizing one of three expert modes of the Russian current. The electrically elicited quadriceps muscle extensor torque

will be measured in response to modes at the participants' maximum tolerance at three points before the start of training, after three weeks of training, and at the six-week follow-up by the Biodex isokinetic system.

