## **2.5 Randomization**

Randomization will be used to determine which mode the participant will receive. The randomization sequence for our three groups of interest (Off mode, Rest mode, and On2 mode) will be computer-generated by one of the investigators who will not be involved in the volunteer recruiting the sequence will then be blocked (block sizes of 4, 6, and 8, in random order). The allocation will be hidden in sequentially numbered, sealed, opaque envelopes. The participants will be stratified by their gender (female or male).

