contraction, with 0 indicating "no pain" and 10 the "worst pain imaginable." Participants will be informed that a pain level of 7/10 is the maximal acceptable pain, If the pain rating reaches 7/10 or if they decide to discontinue testing for any other reason, the trials will be discontinued immediately. Similarly, the participants will be instructed to stop stimulation at a similar level of discomfort. Individuals will be submitted to the following 3 randomized test conditions, and the electrically RC elicited isometric knee extensor torque will be measured in response to each of the modes at the participants' maximum tolerance. RC stimulation session will last for 15 minutes. The Russian current neuromuscular electrical stimulation will be administered using a Chattanooga Forte 200 Combo stimulator (DJO Global, Vista, CA). The Russian currents produce 50 bursts per second at a carrier frequency of 2500 Hz, with each burst lasting 10 milliseconds and followed by a 10-millisecond inter-burst gap, resulting in a 50% duty cycle and a 200-microsecond phase duration as a fixed parameter. which automatically adjust the 3 expert modes:

OFF mode;

ON2mode; consists of two intervals the stimulus will be applied as; preset on the device, following by 2 second off and then and ON2 stimulus that has a frequency of 50 Hz and 100% amplitude.

Rest mode; consist of two intervals the stimulus will be applied as; preset on the device, then follow by a continuous Rest stimulus that has a frequency of 24 Hz and 83% amplitude.

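### The inputs in section 2.7 do not give 66 participants for a three-arm parallel comparison; with 66, pairwise power is about 46%, not 80%

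*Protocol*

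**What the plan says.** Section 2.7 of the protocol states: "The required sample size was calculated by assuming 80% power with a significance level of 0.05". It continues: "To detect the minimum mean difference of 1.5 points and a standard deviation of 2.5 and considering a 10% dropout". It names quadriceps torque as the outcome being sized and refers to a pilot study. It gives no test, sidedness, type of SD, number per arm or total.

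The total is in the Methods part of the abstract: "Sixty-six healthy university students will be recruited from the University of Sharjah". The same paragraph fixes the design: "The volunteers will be divided into three systemically randomized experimental groups", and "Each group will be admitted to a program of training utilizing one of three expert modes of the Russian current". Section 2.5 agrees: "The randomization sequence for our three groups of interest (Off mode, Rest mode, and On2 mode) will be computer-generated". Section 2.6 also describes assignment to three groups. The allocation ratio is not stated.

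**The concern.** The hypothesis and the primary objective compare modes, and each group trains with one mode, so the calculation has to size a comparison between independent arms. A standardized difference of 1.5/2.5 = 0.60 is moderate, and 22 participants per arm looks far too few to detect it with 80% power. If so, the stated power is one that the trial does not have. A null result for the modes would then be read as evidence of little difference, although the design had less than an even chance of detecting the difference it was planned for.

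**Working it through.** **Inputs.** Difference 1.5, SD 2.5, power 80%, alpha 0.05 and dropout 10% (section 2.7); total 66 and three groups (abstract, Methods). Assumed, because not stated: equal allocation (22 per arm), two-sided alpha, and 2.5 as the between-participant SD of the analysed value. With 10% dropout, 66 × 0.9 = 59.4, or about 20 evaluable per arm.

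**Can 66 be reproduced?** Not by any between-arm formula tried:

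| Calculation | Evaluable | After 10% dropout |
|---|---|---|
| Two-sample, two-sided, normal: 2 × (1.96 + 0.84)² × (2.5/1.5)² = 43.6, so 44 per arm | 132 | 147 |
| Same, t-test: 45 per arm | 135 | 150 |
| Two-sample, one-sided, normal: 35 per arm | 105 | 117 |
| Bonferroni over three pairs, normal: 59 per arm | 177 | 198 |
| One-way ANOVA, third mean equal to one of the others | 126 | 140 |
| One-way ANOVA, third mean midway | 165 | 184 |

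The total 66 does appear if each group is sized by a one-sample or paired formula: (1.96 + 0.84)² × (2.5/1.5)² = 21.8, so 22, and 3 × 22 = 66. That has no dropout allowance; with one, 22/0.9 gives 25 per group, or 75. Other routes also reach 66: a one-sided one-sample t-test needs 19, 19/0.9 gives 22, and 3 × 22 = 66; or simply 60 × 1.1 = 66. None of these sizes a difference between arms.

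**Power of 66 for a difference of 1.5.** At 20 per arm the noncentrality is 1.5/(2.5 × √(2/20)) = 1.90; at 22 per arm it is 1.99.

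| Test | 20 per arm | 22 per arm |
|---|---|---|
| One pair, two-sided t | 45.6% | 49.4% |
| One pair, one-sided t | 58.7% | 62.3% |
| One pair, two-sided t, Bonferroni over three pairs | 28.5% | 31.9% |
| Omnibus F, third mean midway | 36.1% | 39.5% |
| Omnibus F, third mean equal to one of the others | 46.5% | 50.7% |

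**Detectable difference.** At 20 per arm, a two-sided t-test has 80% power for 2.27, which is 2.27/2.5 = 0.91 SD.

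**Baseline adjustment.** Adjusting for a baseline value with correlation r reduces the SD to 2.5 × √(1 − r²). Power at 20 per arm for one unadjusted pair is then 57.0% at r = 0.5, 73.5% at 0.7, 79.8% at 0.75 and 86.9% at 0.8. A correlation of about 0.75 is needed for 80%.

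**The case against.** The strongest objection is that the 46% rests on choices the protocol does not make. Section 2.7 does not say whether 2.5 is the SD of raw values, of changes or of paired differences, and it names no test. This stands as a reason to give the power as a range with its assumptions. It does not restore 80%, because even the one-sided reading gives about 59% at 20 per arm.

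A second objection is that section 2.9 describes individuals undergoing three randomized conditions, with torque measured under each mode, and that the secondary objective in section 2.4 rates discomfort per mode condition. If every participant received all modes and 2.5 were the SD of paired differences, 60 completers would give about 99.5% power. But the abstract and sections 2.5 and 2.6 describe one mode per group, and a paired design with these inputs would need only 24 participants by t-test (27 with dropout), so 66 is not its result either. What stands is that the two descriptions conflict and must be reconciled.

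Third, baseline adjustment could recover the power. It could, but only with a correlation near 0.75, for one unadjusted pair, and under an analysis that the protocol does not describe.

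A reader might also infer more than the text supports:
- **That a paired formula was used and dropout was forgotten.** The protocol shows no formula, and one of the routes to 66 does include dropout.
- **That the 1.5 points come from the 0–10 pain scale.** Section 2.7 names torque, and section 2.9 normalizes elicited torque to a percentage of KEMVIT, so percentage points are a natural reading. Only the missing unit is a fair criticism.
- **That 1.5 lies within the 5% tolerance in section 2.9.** That 5% is a rule for repeating maximal contractions, not an error margin for a group difference.
- **That reference 25, a methods textbook, contradicts the pilot study.** The text does not say that the reference is the pilot.

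**Conclusion.** The concern holds as a mismatch between the stated inputs and the stated total. Under a parallel three-arm design with equal allocation and 2.5 as the between-participant SD, the inputs require about 150 randomized for a two-sided pairwise comparison, and the plan has 66. Its pairwise power is about 46% after the planned dropout, and 29% to 59% across the choices of multiplicity and sidedness. The one-sample or paired origin of 66 is plausible but inferred, and the conclusion does not depend on it. This should be corrected before the power statement is relied on.

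**What to change.** Keep 66 and rewrite section 2.7:

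1. State that 66 randomized, about 20 evaluable per arm, gives about 46% power for a difference of 1.5 with SD 2.5 (two-sided 0.05, one pairwise comparison), or 80% power for a difference of about 2.3.
2. Name the between-arm test, its sidedness and any multiplicity adjustment. Say whether the SD is of raw values, changes or paired differences, and give the number per arm and the total in the same place.
3. Give the difference and the SD in the unit of the primary torque outcome, either Nm or percentage points of KEMVIT. If that changes the inputs, recompute the figures in item 1.
4. Reconcile the three-condition wording in section 2.9 with the parallel-group description in the abstract and sections 2.5 and 2.6.
5. Claim a gain from baseline adjustment only if that analysis is specified and the pilot supports the correlation used, and state that correlation.

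The cost is a rewording and one recalculation, and the stated power becomes less favourable. No extra participants are needed. Rewording does not raise the power: the trial would remain under-powered for 1.5 unless item 5 can be justified, and the report should interpret a null result accordingly.

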## **2.8 Ethical consideration.**

This research was approved by the Research Ethical Committee (REC)/UOS (REC-22-02-28-S) on February 28, 2022, and registered at [www.clinicaltrials.gov](http://www.clinicaltrials.gov) (NCT05303181) on March 21, 2022. Consent forms will be distributed to participants prior to data collection and the general medical questionnaire. The participants will be informed that their data will be used for the study only. Privacy and confidentiality will be maintained by using a coding system for data. The data will be stored on a locked-password-required computer in the primary investigator's office and will be accessed by the study's researchers only. Participation in this study is completely voluntary. The participant has the right to leave the study at any time. This will not result in any penalty or loss of benefits to which they are entitled. If the participant decides to withdraw, any data taken from him will not be used in the research and will be destroyed.

## **2.9 intervention**

Prior to testing, the participant's blood pressure will be taken at rest in accordance with the American College of Sports Medicine guidelines for exercise; participants will be disqualified if their resting blood pressure is greater than 180 mmHg systolic or 110 mmHg diastolic. A 5-minute warm-up on a cycle ergometer with a low-intensity warm-up will be required to reduce the possibility of muscle strain during testing. Participants then sit in a Biodex System 3 force dynamometer (Biodex Medical Systems, Inc., Shirley, NY) which will be calibrated before the session starts. To prevent excessive trunk movement, the participant will be tightly attached to the seat with three non-elastic straps: two diagonally across the chest straps from shoulder to contralateral hip and one waist strap at the level of the anterior superior iliac crests. The dynamometer will be adjusted to an angular velocity of 0°/s (isometric mode) for all tests, and the dominant limb will be in a 90° knee flexion position, which will be measured by the dynamometer's goniometer. To secure the distal leg, the lever arm of the dynamometer will be

positioned just above the ankle malleoli, while the lateral epicondyle of the knee will be in line with the axis of rotation of the lever arm. The participant's peak knee extension torque will be determined using an MVIC performed at 90° of knee flexion against the isokinetic dynamometer's resistance arm. After being correctly seated in the Biodex device, and prior to the application of stimulation, participants will be asked to perform a minimum of three maximum voluntary isometric contractions (MVIC). The participant is required to hold each contraction for around five seconds and rest for 120 seconds (about two minutes) in between each contraction. The highest peak torque generated during the three maximum-effort trials will be called KEMVIT, where the maximum volitional peak knee extensor muscle torque (Newton meters) will be recorded using a Biodex as a baseline measurement. For instance, if there is an increase in the maximum torque by more than 5% on the third attempt, the participants will be asked to continue the contraction efforts until the increase in maximum peak torque decreases to less than 5%. The peak torque produced during the testing will be used to normalize the RC-elicited knee extensor torque to produce a percent of KEMVIT (%KEMVIT), a verbal encouragement will be given to the participants by the examiner to promote maximal effort during all contractions.

In the same position used to determine the maximum torque, RC stimulation will be administered. Two channels will be used for delivering the electrical stimulus: On the anterior thigh, four circular cutaneous electrodes with a 7.6-cm diameter will be placed. The anode will be positioned distally over the vastus medialis, with the cathode being positioned proximally over the rectus femoris. Prior to beginning testing, participants will be instructed to relax during the electrical stimulation application so that all knee extensor torque production comes directly from the electrical stimulation rather than the quadriceps muscle voluntary contraction. Participants will be monitored and instructed to self-report pain on an 11-point (0–10) numeric pain-rating scale after each

contraction, with 0 indicating "no pain" and 10 the "worst pain imaginable." Participants will be informed that a pain level of 7/10 is the maximal acceptable pain, If the pain rating reaches 7/10 or if they decide to discontinue testing for any other reason, the trials will be discontinued immediately. Similarly, the participants will be instructed to stop stimulation at a similar level of discomfort. Individuals will be submitted to the following 3 randomized test conditions, and the electrically RC elicited isometric knee extensor torque will be measured in response to each of the modes at the participants' maximum tolerance. RC stimulation session will last for 15 minutes. The Russian current neuromuscular electrical stimulation will be administered using a Chattanooga Forte 200 Combo stimulator (DJO Global, Vista, CA). The Russian currents produce 50 bursts per second at a carrier frequency of 2500 Hz, with each burst lasting 10 milliseconds and followed by a 10-millisecond inter-burst gap, resulting in a 50% duty cycle and a 200-microsecond phase duration as a fixed parameter. which automatically adjust the 3 expert modes:

OFF mode;

ON2mode; consists of two intervals the stimulus will be applied as; preset on the device, following by 2 second off and then and ON2 stimulus that has a frequency of 50 Hz and 100% amplitude.

Rest mode; consist of two intervals the stimulus will be applied as; preset on the device, then follow by a continuous Rest stimulus that has a frequency of 24 Hz and 83% amplitude.

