Although, there has been a many studied that investigate the impact of several parameters on the quadriceps muscle's EIT, but no research demonstrates the relationship between expert modes and the increase electrically induced isometric quadriceps torque during the application of burst modulated alternating current at a specific peak current intensity. Since NMES is widely used to strengthen the quadriceps muscle, the impact of expert RC electrical stimulator modes on electrically induced quadriceps forces may offer further data to assist physicians in choosing the best stimulation parameters. Accordingly, this study's aim is to determine the electrically induced torque responses of the quadriceps to three expert types of burst-modulated alternating current at a particular peak current intensity. The results of this study could aid practitioners in using various parameters to improve muscle training at current amplitudes. With understanding of how different modes affect the intensity of muscular training, the physician could be able to provide the most effective NMES strength-training program.

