**Secondary outcome measures**

The secondary objective will be to assess the degree of discomfort experienced by participants for each mode condition at the current amplitude.

[figure not shown]

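### Discomfort by mode is to be rated at an amplitude that discomfort itself sets, so similar ratings would not show that the modes are equally comfortable

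*Protocol*

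**What the plan says.** Section 2.4 (Secondary outcome measures) sets the secondary objective as to "assess the degree of discomfort experienced by participants for each mode condition at the current amplitude". It gives no current value, no percentage of maximal voluntary torque and no intensity common to the modes.

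Section 2.9 supplies the procedure. "Participants will be monitored and instructed to self-report pain on an 11-point" scale after each contraction, and they are told that 7 is the most they should accept. Then: "If the pain rating reaches 7/10 or if they decide to discontinue testing for any other reason, the trials will be discontinued immediately". The next sentence adds that "the participants will be instructed to stop stimulation at a similar level of discomfort". The modes are tested at each participant's maximum tolerance. The Methods part of the abstract agrees ("maximum tolerance at three points before the start of training, after three weeks of training, and at the six-week follow-up"), as does the primary objective, which is to "compare the electrically elicited knee extensor torque at the maximal stimulation tolerance level".

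The Introduction states a different aim: torque responses to "three expert types of burst-modulated alternating current at a particular peak current intensity". That intensity has no value, and section 2.9 does not use it. The fixed stimulation settings listed in 2.9 (carrier frequency, bursts, duty cycle, phase duration) do not include an amplitude. The 100% and 83% figures for the ON2 and Rest stimuli are relative, so they do not set a current.

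**The concern.** If stimulation is raised until discomfort reaches a target, discomfort at that point mostly reproduces the target. The stop at 7/10 and the instruction to stop at similar discomfort both make discomfort the end point of the titration, and section 2.4 then names it as an outcome. A mode that hurts more per unit of current would be stopped at a lower current with much the same rating.

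Section 3.1 offers the findings to physiotherapists who want high torque with less discomfort. Torque at tolerance, the primary outcome, answers part of that question. A rating taken at tolerance adds little to the rest, and similar ratings could be mistaken for equal comfort.

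**Working it through.** The protocol has no discomfort figure to reproduce: no expected difference, no standard deviation, no current step and no device maximum. The check is therefore the logic of the stop rule, with sizes from an assumed model.

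**Logic.** Let the rating be k × c, where c is the current and k is a person's pain per unit of current. In a harsher mode k becomes m × k. A person stops when the rating reaches a personal limit L.
- Stopping current: L/k in the reference mode and L/(m × k) in the harsher mode. The ratio is 1/m.
- Rating at the stop: L in both modes, so the difference is 0 if the current rises smoothly.
- Rating difference at a common current where the reference rating is 4: 4 × (m − 1). For m = 1.10, 1.25 and 1.50 this is 0.4, 1.0 and 2.0 points.
- Tolerated current falls by 1 − 1/m, which is 9%, 20% and 33%.

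**Two departures from zero.**
- Overshoot: pain is rated after the contraction, so the last rating can pass the limit. If current rises in steps of s (one unit raises a typical reference rating by one point), the mean overshoot is about m × s/2, and the modes differ by about (m − 1) × s/2. For s = 1 this is 0.05, 0.125 and 0.25. For s = 2 it is 0.10, 0.25 and 0.50.
- Device maximum: people who reach it before their limit are rated at a common current, so their difference survives.

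**Simulation of the same model.** Assumptions: k lognormal with median 1 and log-SD 0.3; ratings rounded to whole points; 80% with a limit of 7 in the coarser-step rows and 50%, 80% or 100% in the others; the remaining people with limits of 4 to 6. Entries are the mean rating difference, harsher minus reference.

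| Rated at | m = 1.10 | m = 1.25 | m = 1.50 |
|---|---|---|---|
| Common current, reference rating about 4 | 0.4 | 1.0 | 2.0 |
| Stop, steps of 0.25, nobody at device maximum | 0 | 0 | 0 |
| Stop, steps of 1, nobody at maximum | 0.05 | 0.12 | 0.24 |
| Stop, steps of 2, nobody at maximum | 0.09 | 0.25 | 0.47 |
| Stop, steps of 0.25, 10% at maximum | 0.06 | 0.11 | 0.14 |
| Stop, steps of 0.25, 20% at maximum | 0.12 | 0.23 | 0.29 |
| Stop, steps of 0.25, 40% at maximum | 0.2 | 0.45 | 0.6 |

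The share that survives runs from 0 to 0.2/0.4 = 50%, the top figure needing 40% of participants at the device maximum. With steps of 1 it is about 12% (0.24/2.0), and with steps of 2 about 24% (0.47/2.0).

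**A second model**, with straight-line pain curves, random error and 22 per group (66/3), gave the same picture. A true difference of 1.5 points between the extreme modes was observed as 0.06 to 0.09 at the stop, and one of 2.5 points as 0.12 to 0.13. A one-way ANOVA rejected in 5 to 6% and 5 to 12% of runs. At a common amplitude it rejected in 37 to 42% and 82 to 83%.

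**One mode or three.** Section 2.5 says "Randomization will be used to determine which mode the participant will receive", while 2.9 can be read as testing everyone under all three. The stop rule acts on each test, so the result is the same either way.

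**The case against.** **The amplitude is ambiguous.** Section 2.4 does not say that discomfort is rated at tolerance, and the Introduction names a common intensity. This stands as far as it goes: the text holds an unresolved conflict. But section 2.9 is the only procedure given, and followed as written it yields ratings at tolerance.

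**Ratings follow every contraction, so the last one need not be the outcome.** True. Earlier ratings could be compared across modes only if the current were recorded with them. No section asks for that, although a case report form might. Asking for it in the protocol settles the matter.

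**The figures are assumed.** They are. One multiplier on pain per unit of current is also a crude picture of modes that differ in what follows the preset stimulus. The direction follows from the stop rule; the sizes do not.

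**No discomfort test is named.** Section 2.10 specifies no comparison of discomfort between modes, and nothing says that similar ratings will be read as equal comfort. The risk lies in how the result is used, which is why the fix includes a statement on interpretation.

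**Stronger readings that the document does not support.** A reader might infer that ratings cannot exceed 7. They can, because 7 triggers the stop only after a contraction has been rated. A reader might infer that no difference can survive; overshoot and the device maximum both let some through. A reader might also infer that a harsher mode would look gentler because people leave it early. That needs stopping habits that differ by mode, for which the protocol gives no evidence.

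**Conclusion.** The point holds as one of heavy attenuation. Under section 2.9, discomfort ratings are drawn together across modes whatever the true difference at equal current, so similar ratings would say little about relative comfort. In the assumed models, between none and about half of a true difference survives, and about a quarter or less when nobody reaches the device maximum and steps are no larger than 2 units. These sizes rest on an assumed pain-current relation, current step and share at the device maximum.

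The primary outcome is not affected: torque at a matched tolerance limit is a valid comparison. The 7/10 limit protects participants and should stay. This concerns a secondary outcome, but it is the trial's only stated measure of discomfort, and it should be corrected in the protocol because later analysis cannot supply currents that were not recorded.

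**What to change.** Keep the 7/10 limit, the stop rule and the primary torque measure. Then:

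1. In section 2.9, record the stimulation current with each pain rating, and the current and reason at the stop (7/10, the participant's own earlier stop, or device maximum).
2. In section 2.4, define the secondary outcome as the current tolerated at the stopping point, and report by mode how many participants reach the device maximum.
3. State that similar ratings at tolerance will not be read as equal comfort.

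The cost is one extra recorded value per rated contraction and edits to 2.4 and 2.9. There is no extra stimulation and no participant is lost.

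If ratings at a common current are preferred, which is closer to the Introduction's aim, pre-set one low current below the limit. State that it is the device's preset (100%) amplitude, and say which interval of ON2 and Rest is rated, since Rest continues at 83%. Report by mode how many do not reach it. This costs one extra rated contraction per test and gives no rating for the least tolerant participants. In the first assumed model, a current with a median reference rating of 2 is reached by 96 to 100% of participants, one of 3 by 76 to 100%, and one of 4 by only 47 to 97%. At level 4 that loss shrinks the 2.0-point difference (m = 1.50) to about 1.2. At level 2 almost none of its 1.0-point difference is lost.
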